### Statistical methods

Differences in baseline characteristics between patients undergoing or not undergoing yearly standardised imaging surveillance by either CTA or DUS, will be analysed using the χ^2^ or Fisher's exact test for categorical variables and the student's t-test or Mann-Whitney test for continuous variables, if appropriate.

The primary endpoints, that is, survival and freedom from intervention will be estimated by Kaplan-Meier survival analysis and differences between groups will be assessed with the log-rank test.

Secondary endpoints such as freedom from aneurysm rupture between patients with and without yearly standardised imaging surveillance will be estimated by Kaplan-Meier survival analysis, and differences between these groups will be calculated with the log-rank test.

Multivariable cox regression analysis will be used to determine survival and the freedom of intervention corrected for age, gender, AAA diameter, ASA classification, neck length, neck angulation and type of endograft. The association between postoperative intervention and the following covariates will be investigated with the multivariate Cox-regression analysis:

Age.Gender.AAA diameter.ASA classification.Neck length (>15 mm).Neck angulation (>60°).Type of endograft.Initial postoperative CTA.

All statistical analyses will be done with SPSS software (IBM, V.25). The level for statistical significance is set at a p value <0.05. The proportion of missing data will be displayed. The missing values will be imputed by multiple imputation techniques if this does not exceed 10%–15% and conduct a sensitivity analysis to investigate the effect of the missing data on the results of the analysis. If missing data on outcome variables exceeds 15%, we plan to perform subgroup analysis.

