## Abstract

**Introduction:**

Strict imaging surveillance protocols to detect complications following endovascular aneurysm repair (EVAR) are common practice. However, controversy exists as to whether all EVAR patients need intense surveillance. The 2019 European Society for Vascular Surgery guidelines for management of abdominal aortic aneurysm (AAA) suggest that patients may be considered for limited follow-up with imaging if classified as ‘low risk’ for complications based on their initial postoperative imaging. The current study aims to investigate the intervention-free survival and overall survival stratified for patients with and without yearly imaging surveillance.

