**Methods and analysis:**

The Observing a Decade of Yearly Standardised Surveillance in EVAR patients with Ultrasound or CT Scan study comprises a national multicentre retrospective cohort study in 17 medical centres. Consecutive patients with an asymptomatic or symptomatic infrarenal AAA who underwent EVAR between January 2007 and January 2012 will be included in this study with follow-up until December 2018. Clinical variables and all follow-up information will be retrieved in extensive data collection from the patient’s medical records. In addition, an e-survey was sent to vascular surgeons at the 17 participating centres to gauge their opinions regarding the possibility of safely reducing the frequency of imaging surveillance. Primary endpoints are intervention after EVAR and aneurysm-related mortality. The initial estimated sample size is 1997 patients.

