### Primary and secondary endpoints

#### Main study endpoint

The number of patients with an intervention and aneurysm-related mortality classified for patients with and without yearly imaging surveillance.

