### Study procedures

The primary outcomes of this study are interventions and aneurysm-related mortality for patients who had a normal initial postoperative CTA and who do adhere to our definition of yearly imaging surveillance over a 6-year to 11-year follow-up period, compared to those who do not adhere to our definition.

Interventions are EVAR-related interventions defined by the SVS reporting standards as postoperative adjunctive manoeuvres.^16 17^ Interventions for wound complications at the access site are not included, since these are detectable without the use of imaging.

Date of death during follow-up, if applicable, will be obtained from patient medical records and verified by the Dutch municipal personal records database (GBA).

Details of all surveillance imaging are obtained from patient medical records and radiology reports. The time between imaging appointments is calculated to determine whether patients adhere to this studies definition of with yearly imaging surveillance, that is, within every 16 months.

Date, type, indication and outcome of all postoperative imaging during follow-up are obtained from patient medical records, specifically imaging order forms and radiology reports. A normal initial postoperative CT scan is defined as a CT scan which shows no endoleaks, endograft migration (>10 mm), kinking or obstruction. All imaging outcomes are based on the report compiled by radiologists. These reports will not be re-evaluated by an independent radiologist, since we want to base our outcomes on real life data.

Secondary outcomes are all-cause mortality, type I, type II, type III and type IV endoleak, graft or outflow (iliac) occlusion, aneurysm rupture and endograft infection. This is also obtained from patient medical records, specifically radiology reports and Dutch municipal personal records database (GBA).

Date of aneurysm rupture is obtained from patient medical records, specifically operative reports, radiology reports and progress notes.

Costs of all EVAR-related imaging and outpatient clinic visits will be calculated per patient. Cost is defined as volume times price. Prices from the ‘Cost manual of the Dutch Health Care Institute’’ will be used. Costs for the patients will also be included. The quality-adjusted life years, a generic measure of disease burden including both the quality and quantity of life, cannot be calculated with this retrospective design.

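### The statistical methods name survival as a primary endpoint where the rest of the protocol names aneurysm-related mortality, so one of the two sized primary endpoints has no stated analysis

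*Protocol article*

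**What the plan says.** Three places in the protocol article define the primary endpoints, and they agree:

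- Abstract, Methods and analysis: "Primary endpoints are intervention after EVAR and aneurysm-related mortality".
- Main study endpoint: "The number of patients with an intervention and aneurysm-related mortality classified for patients with and without yearly imaging surveillance".
- Study procedures: "The primary outcomes of this study are interventions and aneurysm-related mortality for patients who had a normal initial postoperative CTA".

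Study procedures then gives all-cause death a different rank: "Secondary outcomes are all-cause mortality, type I, type II, type III and type IV endoleak".

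Sample size and power treats aneurysm-related mortality as a sized endpoint in its own right. It is a non-inferiority comparison with a 3-point margin, one-sided 0.05 and 80% power, giving 653 per group and 1813 patients after inflation. It comes after the calculation for interventions, which gives 719 per group and 1997 in total.

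Statistical methods restates the primary endpoints differently: "The primary endpoints, that is, survival and freedom from intervention will be estimated by Kaplan-Meier survival analysis". Groups are compared with the log-rank test. The adjusted analysis follows the same pair: "Multivariable cox regression analysis will be used to determine survival and the freedom of intervention corrected for age, gender, AAA diameter". Aneurysm-related mortality, the 3-point margin and non-inferiority do not appear in that section.

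The aim in the abstract's Introduction gives another pairing: to "investigate the intervention-free survival and overall survival stratified for patients with and without yearly imaging surveillance".

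**The concern.** This is more than a detail left to a separate analysis plan. The section states what the primary endpoints are, and one of the two differs from the definition given three times elsewhere. Whoever writes or runs the analysis must choose which section to follow.

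The study's argument is about safety. The Discussion expects fewer interventions and no difference in aneurysm-related mortality with less intensive follow-up. If Statistical methods is followed literally, the mortality half of that argument is tested on death from any cause, where aneurysm deaths are diluted by all the others. The comparison that was sized has no named analysis. The study is retrospective and its outcomes have already occurred, so uncertainty over which mortality endpoint was fixed in advance weakens whatever is reported.

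**Working it through.** **Step 1. Which endpoint holds which rank**

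| Section | Mortality endpoint | Rank |
|---|---|---|
| Abstract, Methods and analysis | aneurysm-related | primary |
| Main study endpoint | aneurysm-related | primary |
| Study procedures | aneurysm-related | primary |
| Study procedures | all-cause | secondary |
| Sample size and power | aneurysm-related | sized, second of two |
| Statistical methods | survival, unqualified | primary |
| Abstract, Introduction | overall survival | stated aim |

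Statistical methods is the only section that attaches the word primary to survival.

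**Step 2. Reproduce the plan's figures**

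*Aneurysm-related mortality.* Inputs from Sample size and power: 0.95 free of aneurysm-related death at 7 years in both groups, margin 0.03, one-sided 0.05, power 80%.

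n per group = (z₀.₉₅ + z₀.₈₀)² × 2p(1−p) / margin²
= (1.6449 + 0.8416)² × 2 × 0.95 × 0.05 / 0.03²
= 6.1826 × 0.095 / 0.0009 = 652.6, so 653. This matches exactly.

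Inflation: 1306/0.8 = 1632.5, and 1632/0.9 = 1813.3. Both match after truncation. The same paragraph also mentions 0.97, but 0.97 in both groups gives 400 per group, so 653 rests on 0.95.

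*Intervention.* Inputs: 0.75 versus 0.82, 90% power, 0.05 taken as two-sided.

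n per group = (1.9600 + 1.2816)² × (0.75 × 0.25 + 0.82 × 0.18) / 0.07²
= 10.507 × 0.3351 / 0.0049 = 718.6, so 719. This matches.

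Inflation: 1438/0.8 = 1797.5, taken as 1798, and 1798/0.9 = 1997.8. The total of 1997 therefore comes from interventions, and 1813 from aneurysm-related mortality.

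**Step 3. Non-inferiority power at 719 per group, aneurysm-related mortality**

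Power = Φ(margin/SE − 1.6449), with SE = √(2p(1−p)/719).

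p = 0.95: SE = √(0.095/719) = 0.01150; 0.03/0.01150 = 2.610; Φ(0.965) = 0.833.

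**Step 4. The same margin and alpha applied to all-cause survival**

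The protocol gives no all-cause rate. I assume 50-70% survival at 7 years, equal in both groups.

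| 7-year survival (assumed) | SE at 719 per group | Power at 719 | n per group for 80% |
|---|---|---|---|
| 0.50 | 0.02637 | 0.306 | 3435 |
| 0.60 | 0.02584 | 0.314 | 3298 |
| 0.70 | 0.02417 | 0.343 | 2886 |

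Even at an assumed 90% survival, power is about 60% and 1237 per group would be needed. With 5% aneurysm-related mortality, aneurysm deaths would be 5/50 = 10% of all deaths at 50% survival and 5/30 = 17% at 70%.

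**Step 5. The stated test against the sizing**

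The sizing is one-sided non-inferiority with a margin. The only unadjusted test stated is a log-rank test of difference, with significance at p<0.05. A non-significant log-rank result does not show that an excess of 3 points has been excluded. Changing the endpoint's name without changing the test would leave this mismatch in place.

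**The case against.** The best defence is that *survival* is loose shorthand for survival free of aneurysm-related death. The word is unqualified in Statistical methods, while the definitions, the hypotheses and the conclusion of the Discussion all name aneurysm-related mortality. That is a possible account of how the text arose, but nothing in the section says so, and the abstract's aim qualifies the word as overall survival. If shorthand was meant, the same correction is needed.

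Some stronger readings are tempting, and the protocol does not support them:

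- *The endpoint that sets the study's size has no analysis.* The total of 1997 comes from interventions, which do have one. Aneurysm-related mortality is the second sized endpoint.
- *Every defining section makes all-cause mortality secondary.* Only Study procedures says so outright. The list of secondary endpoints includes date of death, and the other definitions are silent.
- *All-cause death is confounded with attendance because frail patients stop attending.* The protocol does not say this. The reasons for missed visits that surgeons reported in its survey are forgotten appointments and force majeure.
- *Intervention-free survival in the abstract is a composite with death.* The term is not defined, and it may mean only freedom from intervention.
- *Power for aneurysm-related mortality is only about 64%.* That is a two-sided test of difference, 95% versus 92% at 719 per group. The comparison that was sized has about 83%.

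None of this removes the contradiction between Statistical methods and the three definitions.

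**Conclusion.** The contradiction stands in the current text. Statistical methods puts survival where the protocol's own definitions put aneurysm-related mortality, in both the log-rank and the Cox analysis. Followed literally, a primary endpoint has no stated analysis and a secondary one is tested in its place.

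The consequence for power is a fall from about 83% to about 31-34% at 719 per group. This rests on three assumptions: 50-70% all-cause survival at 7 years, which is mine; equal groups of 719, as the plan assumes; and the 3-point margin and one-sided 0.05 carried over from aneurysm-related mortality for illustration only. The contradiction itself rests on none of them.

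A reader might infer that aneurysm-related mortality will go unanalysed. The protocol does not show that, since a fuller plan may exist. It does show that this section, as worded, directs the primary mortality analysis to a different endpoint.

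**What to change.** 1. In Statistical methods, replace *survival* with *aneurysm-related mortality* in the statement of the primary analysis and in the adjusted Cox model.
2. Analyse it as it was sized: the between-group difference at 7 years, with a one-sided 95% confidence bound compared with the 3-point margin. The log-rank test may be reported alongside but should not be the only test.
3. List all-cause survival with the secondary analyses, next to freedom from rupture.
4. Align the aim in the abstract's Introduction with the defined primary endpoints, or mark overall survival there as secondary.

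No sample size changes: 653 per group still applies, and 1997 in total still covers it. The cost is mostly wording. The one piece of work is that cause of death must be classified from the medical records. The sections on endpoints and procedures describe how the date of death is obtained and verified but not its cause. The primary endpoint as already defined requires that classification in any case.

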### Sample size and power

Sample size calculation for this study is based on an expected difference of 7% in the proportions of patients not requiring interventions after 7 years between patients undergoing yearly standardised imaging surveillance (75% intervention-free rate^18^) versus those s not undergoing standardised imaging surveillance(82% intervention-free rate^19^). To detect this difference with 90% power and a 0.05 significance level, 719 patients per group are required and 1438 in total. To correct for the fact that the first CTA of approximately 20% of patients is abnormal, 1798 patients (1438/0.8) are needed.^20 21^ In addition, we expect incomplete data in 10% of the patients which results in a total number of 1997 patients (1798/0.9). With this sample size, we can also detect a 3% difference in aneurysm-related mortality with statistical significance. We chose a one-sided significance level (non-inferiority) of 0.05 and for standard proportion a 95% non-aneurysm-related mortality and thus 5% freedom from aneurysm-related mortality after 7 years: 0.95. For equivalence limit difference, we chose an acceptable difference between groups of 3%, in which if differences in aneurysm-related mortality equals 3%, they are considered non-inferior. Test-expected proportion is then equal to the standard proportion 0.97. Thus, the expected difference is 0, calculated with a power of 80%. This results in 653 patients per group and 1306 patients in total. Since the first CTA of approximately 20% of patients is abnormal, 1632 patients (1306/0.8) are needed. In addition, we expect incomplete data in 10% of the patients which results in a minimum of, 1813 patients (1632/0.9) are needed in total.

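### Intervention and rupture are estimated by Kaplan-Meier with no competing-risk method, so absolute risks are overstated if deaths are censored, and the group difference can be biased either way

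*Protocol article*

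**What the plan says.** All references are to the protocol article.

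- **Statistical methods**, primary: "freedom from intervention will be estimated by Kaplan-Meier survival analysis", with the groups compared by a log-rank test. 
- **Statistical methods**, secondary: "Secondary endpoints such as freedom from aneurysm rupture between patients with and without yearly standardised imaging surveillance will be estimated by Kaplan-Meier survival analysis", again with a log-rank test. 
- **Statistical methods**, adjusted: "Multivariable cox regression analysis will be used to determine survival and the freedom of intervention corrected for age, gender, AAA diameter" and further covariates. 
- **Main study endpoint**: "The number of patients with an intervention and aneurysm-related mortality", compared between patients with and without yearly imaging. 
- **Sample size and power**: the planned difference is in the "proportions of patients not requiring interventions after 7 years", with a "75% intervention-free rate" under yearly imaging and 82% without it.

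No section mentions cumulative incidence or another competing-risk method, and none says how a death enters the intervention or rupture curves. The abstract and the closing paragraph of the Discussion state the aim as intervention-free survival, which is a different quantity. Study procedures says that dates of death are taken from the records and verified in the municipal database.

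**The concern.** A patient who dies cannot later have a first intervention or a rupture. If deaths are censored, Kaplan-Meier in effect assigns those patients the future event risk of the survivors. One minus the curve then estimates the risk in a hypothetical population without death, and this is higher than the share of real patients affected.

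The main endpoint counts patients with an intervention, and the planned effect is an absolute difference in proportions at 7 years. Surgeons would use these absolute figures to decide whether less imaging is acceptable. The gap between the two quantities widens with follow-up, which here reaches 11 years.

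The groups are formed by observed adherence to imaging, so their mortality may differ. In that case the vertical distance between two Kaplan-Meier curves need not match the difference in patients affected.

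**Working it through.** **The plan's own figure.** Inputs from Sample size and power: 0.75, 0.82, 90% power, significance level 0.05 (taken as two-sided, because that reproduces the result).

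n = (1.960 + 1.282)² × (0.75×0.25 + 0.82×0.18) / 0.07² = 10.507 × 0.3351 / 0.0049 = 718.6, so 719 per group. The pooled-variance formula gives 722. The stated 719 reproduces.

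**Inputs for the check**

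- S = 7-year freedom from intervention: 0.75 with yearly imaging (group A) and 0.82 without (group B). Reading these as Kaplan-Meier values is an assumption, because the article does not say how they were estimated.
- D = 7-year probability of death in the absence of intervention. The documents give none, so 20% to 60% is shown.
- Constant hazards: h = −ln(S)/7 for intervention and m = −ln(1−D)/7 for death.

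**Formula.** Cumulative incidence at 7 years = h/(h+m) × (1 − exp(−7(h+m))). Because exp(−7(h+m)) = S(1−D), this equals ln S / (ln S + ln(1−D)) × (1 − S(1−D)).

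**Worked line, D = 40%**

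- A: 0.2877/(0.2877+0.5108) × (1 − 0.75×0.60) = 0.3603 × 0.550 = 19.8%.
- B: 0.1985/(0.1985+0.5108) × (1 − 0.82×0.60) = 0.280 × 0.508 = 14.2%.
- Difference: 5.6 points.

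**Equal mortality in both groups** (differences from unrounded values)

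| D | A (25% by Kaplan-Meier) | B (18% by Kaplan-Meier) | Difference (7.0 by Kaplan-Meier) |
|---|---|---|---|
| 20% | 22.5% | 16.2% | 6.3 |
| 30% | 21.2% | 15.2% | 6.0 |
| 40% | 19.8% | 14.2% | 5.6 |
| 50% | 18.3% | 13.1% | 5.2 |
| 60% | 16.7% | 12.0% | 4.8 |

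**Unequal mortality**

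| D in A | D in B | A | B | Difference |
|---|---|---|---|---|
| 50% | 30% | 18.3% | 15.2% | 3.1 |
| 40% | 30% | 19.8% | 15.2% | 4.6 |
| 30% | 40% | 21.2% | 14.2% | 7.0 |
| 30% | 50% | 21.2% | 13.1% | 8.1 |
| 20% | 40% | 22.5% | 14.2% | 8.3 |

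The difference returns to 7.0 points when mortality in B is about 27%, 40% or 53% against 20%, 30% or 40% in A. Above those values Kaplan-Meier understates the difference, and below them it overstates it.

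**Same intervention hazard in both groups.** If both groups have a 25% Kaplan-Meier risk but mortality is 30% in one and 50% in the other, the proportions affected are 21.2% and 18.3%. They differ by 2.9 points while Kaplan-Meier shows none.

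**Growth with time.** At 11 years with S = 0.75 and D = 40% (both at year 7), one minus Kaplan-Meier is 1 − 0.75^(11/7) = 36%. Cumulative incidence is 0.3603 × (1 − 0.45^(11/7)) = 0.3603 × 0.715 = 26%.

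**If death counts as an event instead.** With D = 40%, the 7-year risk of intervention or death is 1 − 0.75×0.60 = 55.0% in A and 1 − 0.82×0.60 = 50.8% in B. Neither is a count of patients with an intervention.

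**The case against.** **Censoring at death is inferred.** The article never states it. Intervention-free survival, the wording of the abstract and the Discussion, can count death as an event, and Kaplan-Meier is a proper estimator of that composite. This stands as a reason to ask for clarification. It does not rescue the plan: Main study endpoint and Sample size and power describe patients with or without an intervention, the composite would fold deaths into that count, and it would not cover rupture.

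**The size rests on assumptions.** This also stands. The only age stated is the lower limit of 18 years in Table 1. A reader may suppose that the cohort is elderly, but the documents give neither an expected age nor an all-cause mortality. The direction of the error in each group's risk holds for any non-zero mortality under censoring. Only its size depends on the assumed figures.

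**The planned tests are sound.** Log-rank and Cox with deaths censored are valid comparisons of cause-specific hazards, and 719 per group reproduces. A reader might infer that the tests or the sample size fail, and neither does.

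**Aneurysm-related mortality.** A reader might extend the point to the 3-point margin. Statistical methods names Kaplan-Meier for survival, freedom from intervention and secondary endpoints such as rupture. It does not name it for aneurysm-related mortality, and the margin is set out as a comparison of proportions. The documents do not support saying that this comparison is biased.

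**It is a detail for a fuller plan.** Censoring rules often are. The choice of estimator, however, is stated in the article, and it does not match the article's own endpoint.

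**Conclusion.** The point holds for the absolute risks of intervention and rupture, and for risk differences read off the curves. If deaths are censored, each group's risk is overstated. Under constant hazards and an assumed 7-year mortality of 20-60% equal in both groups, the intervention risks fall from 25% to 22.5-16.7% and from 18% to 16.2-12.0%.

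It is tempting to add that the between-group difference is overstated too. That follows when mortality is similar in the groups or higher with yearly imaging. It fails once mortality is sufficiently higher without yearly imaging: at 30% against 40% the bias in the difference vanishes, and at 20% against 40% it reverses. The documents do not show which case applies, so the direction has to be left open.

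This should be corrected before analysis. It concerns which absolute risk is reported and does not invalidate the hypothesis tests.

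**What to change.** 1. State how death is handled in each time-to-event endpoint, and reconcile freedom from intervention with intervention-free survival so that one of them is clearly primary.
2. Estimate intervention and rupture by Aalen-Johansen cumulative incidence with death as a competing event. Take the 7-year risk differences and their confidence limits from these estimates.
3. If aneurysm-related mortality is analysed as time to event, treat it in the same way, with death from other causes competing.
4. Keep the log-rank and Cox analyses, labelled as cause-specific hazard comparisons. Keep Kaplan-Meier for all-cause survival.

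The cost is a little more analysis, possibly outside SPSS, and somewhat lower reported risks. No new dates of death are needed, since these are already collected and verified.

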## Introduction

Endovascular aneurysm repair (EVAR) of the abdominal aorta has become the primary treatment of patients with an abdominal aortic aneurysm (AAA).^1^ Both the Society for Vascular Surgery (SVS) International Guidelines and the instructions for use (IFU) of endograft manufacturers recommend yearly imaging surveillance for all patients after EVAR.^2^ However, if the patient is classified as ‘low risk’ for complications based on initial post-operative imaging, the 2019 European Society for Vascular Surgery (ESVS) guidelines recommend delaying imaging until 5 years after repair.^3^ This movement towards reducing the imaging frequency will benefit patients, medical centres and healthcare costs.

Imaging surveillance by CT angiography (CTA) may increase the attributable lifetime cancer risk of patients, as well as putting them at risk of developing nephropathy due to contrast exposure. If yearly CTA is replaced by duplex ultrasonography (DUS) patients still experience the burden of additional hospital visits. Moreover, compliance with yearly imaging is suboptimal and non-adherence to yearly imaging does not appear to be associated with poorer outcomes.^4 5^

It has been questioned whether yearly imaging is necessary for all EVAR patients, and if a specific group of patients can be identified for which surveillance intervals can safely be extended, as is suggested by the new guideline.^3^ For these reasons, in the Netherlands the Observing a Decade of Yearly Standardised Surveillance in EVAR patients with Ultrasound or CT Scan (ODYSSEUS) study has been designed. In this study of approximately 2000 patients with 6–11 years of follow-up, we aim to determine when, and in which patients, it is safe to deviate from the current annual surveillance protocols.

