### General study design

A multicentre retrospective cohort study in 17 medical centres in the Netherlands. Data will be collected from the medical records of all consecutive patients with AAA who underwent EVAR between January 2007 and January 2012. This selection provides a theoretical length of follow-up of 6–11 years on December 2018. Patients will be divided into three groups: (A) patients without abnormalities at their first postoperative CTA with yearly imaging surveillance, (B) patients without abnormalities at their first postoperative CTA without yearly imaging surveillance and (C) patients with abnormalities at their first postoperative CTA (figure 1). This retrospective design has the advantage of collecting long term follow-up data. The Dutch Dream trial found that the number of interventions starts to rise 4 years after EVAR and the long-term results of the EVAR-1 trial show that EVAR has an early survival benefit but inferior late survival compared to open surgical repair.^13 14^ This is in contrast to the recently published long-term results of the OVER trial in which no difference was observed between EVAR and OSR in the primary outcome of all-cause mortality.^15^ Hence, a prospective study would take approximately 8 to 10 years to gather enough patients with adequate follow-up.

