Our study is subject to limitations due to the nature of administrative data and its retrospective and observational design. As with all studies using administrative data, it allows only the collection of data that was documented in patient medical records. It is also possible that some patients may have transferred to alternative surveillance protocols in different medical centres without our knowledge. The study will assess results in 17 medical centres over 11 years, during which time improvements in endograft and in clinical practice has occurred. Attrition bias due to loss to follow-up represents a threat to the internal validity of our cohort study. The mentioned e-survey has only been sent to participating vascular surgeons, perhaps surgeons participating in the ODYSSEUS study strongly believe that imaging surveillance frequency can be reduced. This may have provided a biased view of post-EVAR follow-up in the Netherlands. However, most of the high-volume EVAR centres in the Netherlands have been included. Another limitation is that no information is retrieved from patients’ medical records about when not to intervene and what the reason was for this decision.

In conclusion, with the ODYSSEUS study we aim to confirm the follow-up protocol of the recent ESVS guideline delaying imaging after 5 years if classified in the low risk group and therefore aim to investigate the intervention-free-survival and aneurysm-related mortality for patients with and without yearly imaging surveillance.

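### The stated group comparison covers all follow-up, while the sample size, the 3% margin and the aims refer to fixed times (5 and 7 years) and to when less imaging is safe

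*Protocol article*

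**What the plan says.** The Protocol article sets its question in terms of time. The Introduction states: "we aim to determine when, and in which patients, it is safe to deviate from the current annual surveillance protocols". The closing paragraph of the Discussion aims to confirm guideline advice on "delaying imaging after 5 years if classified in the low risk group".

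Sample size and power is built on a fixed time: "an expected difference of 7% in the proportions of patients not requiring interventions after 7 years", with 75% intervention-free under yearly imaging and 82% without. The non-inferiority calculation for aneurysm-related mortality also refers to 7 years and allows a 3% difference.

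Statistical methods then says: "The primary endpoints, that is, survival and freedom from intervention will be estimated by Kaplan-Meier survival analysis". To compare the groups on these endpoints, it says that "differences between groups will be assessed with the log-rank test". The adjusted analysis reads: "Multivariable cox regression analysis will be used to determine survival and the freedom of intervention corrected for age", followed by the other covariates. Rupture is handled by the same Kaplan-Meier and log-rank pair. The section names no comparison at 5 or 7 years, no period-specific effect and no use of the 3% margin.

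On follow-up, General study design says: "This selection provides a theoretical length of follow-up of 6–11 years on December 2018".

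**The concern.** A log-rank test and a single Cox hazard ratio each give one summary of the whole follow-up. Neither is a difference in risk at 7 years, neither can be read against a margin set in percentage points at 7 years, and neither says at what time less imaging is or is not safe.

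The mismatch does little harm if the hazard ratio between the two groups with a normal first CTA (A, yearly imaging; B, no yearly imaging) is constant. It matters if the ratio changes. The Study objectives section expects imaging to prompt extra interventions, so fewer early interventions in B are plausible. Later interventions for problems found late are also plausible. A pooled result near 1 could then be taken as support for less imaging although the later years differ.

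**Working it through.** **1. The plan's own figures.** Two proportions, unpooled variance, two-sided 0.05, 90% power:

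n = (1.960 + 1.282)² × (0.75×0.25 + 0.82×0.18) / 0.07² = 10.507 × 0.3351 / 0.0049 = 718.6, so 719 per group, as stated.

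Non-inferiority, one-sided 0.05, 80% power, 0.95 in both groups, margin 0.03:

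n = (1.645 + 0.842)² × 2 × 0.95 × 0.05 / 0.03² = 6.183 × 0.095 / 0.0009 = 652.6, so 653, as stated.

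Both calculations size a difference in proportions at 7 years.

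**2. What a constant effect would imply.** HR = ln 0.82 / ln 0.75 = 0.690. Schoenfeld's formula needs 4 × 10.507 / (ln 0.690)² = 305 events. By 7 years, without losses, 719 × (0.25 + 0.18) = 309 are expected, giving power of 90.4%. Under proportional hazards the log-rank test is therefore adequately powered, and the sample size is not wrong.

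**3. What happens if the effect changes.** Simulation with 719 per group, 2000 runs per scenario, uniform entry over 5 years, and censoring at 6.92–11.92 years (from the calendar dates; the text says 6–11). Group A is 75% intervention-free at 7 years. Assumptions not in the protocol: the period hazard ratios, a cut at year 4, death at 0, 5 or 8% a year, and a baseline hazard that is either flat or doubles after year 4 in both groups. Ranges run over the death rates.

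| HR before / after year 4 | Flat hazard: pooled HR; log-rank p<0.05 | Doubling hazard: pooled HR; log-rank p<0.05 |
|---|---|---|
| 0.69 / 0.69 | 0.69; 89–96% | 0.69; 88–97% |
| 0.69 / 1.00 | 0.83–0.86; 36–39% | 0.88–0.90; 21% |
| 0.50 / 1.50 | 0.94–1.03; 6–10% | 1.10–1.18; 16–49% |
| 0.50 / 2.00 | 1.14–1.28; 23–79% | 1.38–1.50; 88–100% |

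For 0.50 / 1.50, tests split at year 4 show the early saving in 93–99% of runs and the late excess in 79–99%.

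**4. What fixed-time differences would show for 0.50 / 1.50.** Flat hazard h = −ln 0.75 / 7 = 0.0411 a year. Doubling hazard h = −ln 0.75 / 10 = 0.0288 to year 4, then 2h.

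| Year | Flat: A v B free | B − A | Doubling: A v B free | B − A |
|---|---|---|---|---|
| 5 | e^(−5h) = 81.4% v e^(−3.5h) = 86.6% | +5.2 points | e^(−6h) = 84.1% v e^(−5h) = 86.6% | +2.5 points |
| 7 | 75.0% v e^(−6.5h) = 76.6% | +1.6 points | 75.0% v e^(−11h) = 72.9% | −2.1 points |
| 10 | e^(−10h) = 66.3% v e^(−11h) = 63.6% | −2.7 points | e^(−16h) = 63.1% v e^(−20h) = 56.3% | −6.9 points |

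The 5- and 7-year pair shows the advantage shrinking or reversing, which one pooled hazard ratio cannot.

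**5. How far the data reach.** With uniform entry, the share who could be followed to 10 years is (11.92 − 10)/5 = 38%. If deaths run at 4–9% a year, this falls to 0.38 × e^(−0.4) = 26% or 0.38 × e^(−0.9) = 16%.

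**The case against.** **The protocol does not predict a changing hazard ratio.** A reader might infer that it does, because General study design says "the number of interventions starts to rise 4 years after EVAR" and cites a trial in which EVAR did better early and worse late. The documents do not support that reading. The first remark concerns interventions after EVAR overall, and the second compares EVAR with open repair. A rise shared by both groups leaves hazards proportional, and log-rank power then stays at 88–97%. The protocol hypothesises only fewer interventions with less follow-up, with aneurysm-related mortality better (Study objectives) or no different (Discussion). This objection stands, so year 4 is not a change point that the protocol supplies for the group effect.

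**Cancellation depends on chosen inputs.** This also stands: 0.50 then 2.00 does not reliably cancel. The simulation concerns intervention, not aneurysm-related mortality. Nor is a non-significant log-rank test for intervention a success for the protocol, whose hypothesis there is a reduction.

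**Kaplan-Meier curves already show the time course.** They do, and 7-year proportions can be read from them. But the article attaches no comparison, interval or decision to any time point.

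**Such detail belongs in an analysis plan.** Proportional-hazards checks and similar detail commonly do, and their absence is no finding. What remains is that the article names its between-group test, and that test targets a different quantity from the one it sizes.

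**A split analysis has its own bias.** A late-period hazard ratio compares only patients still event-free. If B has fewer early interventions, more susceptible patients remain in B, and the ratio can exceed 1 without late harm. This stands and limits the role of any such analysis.

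**Conclusion.** The point holds as a mismatch between stated aims and stated inference. Two sample-size calculations at 7 years, a 3% margin, a 5-year aim and a question about when are all met by a whole-period test and model that estimate none of them. The curves address time only descriptively.

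The risk of masking is conditional. Under the assumed 0.50 then 1.50 pattern, the pooled hazard ratio is about 0.94–1.18 and the test rejects in about 6–49% of trials, depending on baseline hazard and death rate. Under a constant effect nothing is lost. It would go too far to say that the study will miss late harm, that the protocol expects the group effect to turn at year 4, or that the log-rank test, the Cox model or the sample size is wrong in itself. A 7-year difference alone is no complete safeguard either: in the flat-hazard example it still favours B by 1.6 points.

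**What to change.** In Statistical methods:

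1. Prespecify the A v B difference in cumulative risk at 7 years, with a confidence interval, for intervention and for aneurysm-related mortality. Read the mortality interval against the 3% margin.
2. Report the same difference at 5 years, and at both times for rupture.
3. Keep the log-rank test and the Cox model. Add a time-by-group term or period-specific hazard ratios as a supportive analysis, and state that late-period ratios compare only patients still event-free.
4. Base statements about when imaging can be reduced on the fixed-time estimates, not on the pooled log-rank test alone.

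The cost is a little more analysis and wider intervals at fixed times. No new data are needed, because dates of intervention, rupture and death are already collected. A 10-year contrast is optional, since few patients can be observed that long.
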